#### Secondary Analysis

Independent *t* tests between 2 groups will compare the mean of the HF knowledge score before and at the end of the study. The HFQOL at baseline and at monthly time intervals will be compared by the *P* value correction based on the multiple comparisons.

In order to describe the surveillance, the median of admissions to health care settings will be used. Also, the Kaplan-Meier survival analysis will be applied for a descriptive comparison of the surveillance and, a log-rank test will be used to detect the significance difference between the 2 groups. A hazard ratio will be reported with 95% CI.

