**Objective:**

This study describes a protocol for the self-monitoring daily diaries of weight and shortness of breath (SOB) based on the traffic light system (TLS). The primary objective is to compare the self-care between the intervention and control group. Comparison of HF knowledge, HF quality of life (HFQOL), and all-cause hospitalization between the 2 groups are the secondary objectives.

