##### Quality of Life

Heart failure quality of Life (HFQOL) will be assessed by the Iranian version of the Minnesota Living with Heart Failure Questionnaire (MLHFQ) with Cronbach alpha=.95 [51]. The psychometric properties of the questionnaire were evaluated by Middel et al in 2001 (Cronbach alpha≥.80 for the scales) [52]. The MLHFQ consists of 21 questions with a 6-point Likert scale ranging from 0 (without limitation) to 5 (maximum limitation). It consists of physical and emotional dimensions. The physical dimension is the sum of the question scores (questions 1 to 7, 12, 13) while the emotional dimension is based on questions 17 to 21. Questions 8 to 11 and 14 to 16 are related to lifestyle, financial situations, and side effects of medications. The total is the sum of the 21-question score, and a lower score reflects better quality of life [53]. Since this instrument assesses HFQOL in the previous month [54], we will ask participants to complete MLHFQ by themselves at baseline and then monthly for 3 months.

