### Data Collection

Eligible patients will be asked to read and sign a written informed consent form. The research nurse will then collect demographic and clinical characteristics by participant self-reporting and from a medical chart and then record these in data collection forms (see Table 1). Also, participants will be asked to complete baseline surveys (SCHFI, HF knowledge, HFQOL, and health literacy) by themselves in the HF clinic before randomization.

In order to assess participant health literacy, we will use the Heart Failure-Specific Health Literacy Scale with Cronbach alpha=.71. It consists of 12 items each with 4 possible scores (1 to 4): inapplicable (1) to strongly applicable (4) where a higher score indicates a higher level of health literacy except items 1 to 4 [55]. The Iranian version of this scale was prepared after getting the developer’s permission. Thus, it was first translated into Persian by a forward-backward translation method. Then, face and content validity were approved by an expert’s opinion (nursing faculty, nurse practitioners, and cardiologists) and discussion with patients with HF. A pilot study was conducted to assess the reliability with 30 HF patients and where a Cronbach alpha value of .77 was determined. Deletion of items could not improve the value similar to the original scale. Therefore, we decided to retain all items [55]. We will ask the participants to complete the health literacy scale as a baseline survey.

In order to measure the HF knowledge at the end of the study, monthly self-care behavior, and the HFQOL, the outcome assessor will be blinded to study group assignments. The assessor will send the DHFKS, SCHFI, and MLHFQ to the participants in both groups by telegram mobile application in the morning of each monthly call follow-up and ask them to send answers before 6 pm of the same day.

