#### Primary Analysis

Baseline scores for each scale of SCHFI including self-care maintenance, management, and confidence will be compared in both groups by an independent *t* test. Due to the measurement of self-care behavior at baseline and at monthly time intervals, we will calculate the mean of monthly self-care scores in order to compare the mean of self-care behavior after the intervention in both groups. Also, because of the frequent measurement of self-care behavior, we will also use *P* value correction based on the Bonferroni method [58]. A linear logistic regression procedure will be applied to determine the factors affecting self-care behavior. The odds ratio will be reported with 95% CI.

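### The secondary analysis tests chance baseline differences in knowledge and quality of life, counts the quality-of-life one in its multiplicity correction, and leaves both baseline scores unused as covariates

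*Protocol article*

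**What the plan says.** The abstract's Objective sets the frame: "Comparison of HF knowledge, HF quality of life (HFQOL), and all-cause hospitalization between the 2 groups are the secondary objectives".

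On data collection, the Data Collection section states that "participants will be asked to complete baseline surveys (SCHFI, HF knowledge, HFQOL, and health literacy) by themselves in the HF clinic before randomization". The Quality of Life section asks participants to "complete MLHFQ by themselves at baseline and then monthly for 3 months". Knowledge is measured at baseline and once more at the end of the study.

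On analysis, the Secondary Analysis section makes two statements:

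- **Knowledge.** Independent t "tests between 2 groups will compare the mean of the HF knowledge score before and at the end of the study". The test and the between-group comparison are explicit.
- **Quality of life.** "The HFQOL at baseline and at monthly time intervals will be compared by the" P "value correction based on the multiple comparisons". Baseline is named among the compared time points. No test is named, and neither is the correction method.

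Bonferroni is named only in the Primary Analysis section, for self-care: P "value correction based on the Bonferroni method". No baseline-adjusted analysis is stated for either secondary score. The only regression in the Statistical Methods concerns factors affecting self-care.

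**The concern.** Both scores are taken before randomization. A difference between arms at that point is therefore chance, and a test of it says nothing about the intervention. Two costs follow.

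1. For MLHFQ the baseline comparison sits in the corrected set. It tightens the threshold for the three follow-up comparisons that do carry information on treatment.
2. A follow-up comparison that ignores the baseline score leaves in the outcome the variance that baseline explains. It also lets part of any chance imbalance into the estimate. With about 34 per arm, noticeable imbalances are not rare.

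At stake is the precision of the two patient-reported secondary outcomes. If adjustment is not fixed in advance, there is also a temptation to decide on it after seeing whether the baseline test is significant.

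**Working it through.** **The plan's own figure.** No sample size, effect size or SD is given for MLHFQ or knowledge. The stated 68 is for self-care. Cohen f = 0.168, three measurements, correlation .5, alpha .05 and 80% power give 60 in the within-factor or interaction form of the repeated-measures calculation. Then 60/0.9 = 66.7, so 67, or 68 in equal arms. It serves here only to fix the evaluable number: 34 × 0.9 = 30.6, taken as 30 per arm.

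**Inputs from the protocol.** Significance at .05 (Statistical Methods); 34 per arm and 10% attrition (Sample Size); MLHFQ at baseline and months 1, 2 and 3 (Quality of Life).

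**Assumptions, not in the protocol.** Bonferroni applied to MLHFQ; standardised difference d = 0.5; correlation rho between baseline and follow-up of .3, .5 or .7. The protocol's .5 describes repeated self-care scores, not MLHFQ or knowledge.

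**Step 1: threshold per comparison.**
- Baseline in the family: 0.05/4 = 0.0125.
- Months 1 to 3 only: 0.05/3 = 0.0167.
- With baseline included, the follow-up tests share 3 × 0.0125 = 0.0375 of the 0.05.
- The detectable difference at 80% power rises by the ratio (2.498 + 0.842)/(2.394 + 0.842) = 1.032, that is by 3.2%.

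**Step 2: variance removed by adjustment.** The residual variance factor is 1 − rho². At rho = .3, .5 and .7 it is 0.91, 0.75 and 0.51, so 9%, 25% and 49% of the variance is removed.

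**Step 3: power.** Two-sample noncentral t. Unadjusted noncentrality is d × √(n/2) = 0.5 × √15 = 1.936 on 58 df. Adjusted noncentrality is 1.936/√(1 − rho²) = 2.030, 2.236 and 2.712 on 57 df.

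| Comparison, 30 per arm | alpha | Unadjusted | rho .3 | rho .5 | rho .7 |
|---|---|---|---|---|---|
| MLHFQ per month, baseline in family | .0125 | 27% | 30% | 37% | 56% |
| MLHFQ per month, months 1 to 3 only | .0167 | 31% | 34% | 42% | 60% |
| Knowledge, end of study | .05 | 48% | 51% | 59% | 76% |

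For MLHFQ, removing the baseline test gains about 4 points. Adjustment then gains about 3, 11 or 29 points, so at rho of .5 or more it is clearly the larger gain.

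**Step 4: chance imbalance.** With 34 per arm, the baseline mean difference has a standard deviation of √(2/34) = 0.243 SD. The probability that it exceeds 0.25 SD in either direction is about 30%. In an unadjusted follow-up comparison the expected carry-over is rho times the imbalance, so about half of it at rho = .5.

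**The case against.** **The MLHFQ sentence is loosely worded.** It names no test, does not say the comparison is between groups, and does not say which correction applies. It could describe corrected comparisons between time points, within arms or after a repeated-measures model. This stands as a caution: the between-arm reading rests on the stated objective and on the knowledge sentence beside it. A purely within-arm comparison would not answer that objective, so the wording needs correcting either way. The knowledge sentence has no such ambiguity.

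**A condensed article may leave model details to an analysis plan.** True, and the missing MLHFQ model name is not the point. What is at issue is what the text commits to: baseline as a compared time point under correction, and t tests on knowledge before and after.

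**A reader might infer a much larger loss**, by setting 27% power per month against 59% for one adjusted test at .05. That is not a like-for-like contrast. It also replaces three tests by one, and at d = 0.5 that step alone moves unadjusted power from 31% to 48%. Nothing in the protocol makes testing at several months a fault. The plan also has three chances to show an effect: in simulation with d = 0.5 at each month and a between-month correlation of .5, three unadjusted tests at .0125 detect at least one month about 49% of the time.

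**A reader might also infer** that knowledge loses alpha to its baseline test, or that a chance imbalance passes whole into the estimate. Neither holds. No correction is stated for knowledge, so only the precision point applies there. Imbalance carries over only in proportion to the correlation, and the unadjusted t test remains unbiased over randomization.

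**Conclusion.** The point holds as a matter of efficiency on secondary outcomes. The protocol tests baseline knowledge between arms and lists baseline MLHFQ among the comparisons under correction. It states no use of either baseline score in estimating the treatment effect.

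If the correction is Bonferroni and d = 0.5 with 30 per arm, putting both features right moves MLHFQ power per month from 27% to between 34% and 60%, depending on the baseline correlation. For knowledge, adjustment moves it from 48% to between 51% and 76%. At a correlation of .3 the gain is small. These figures illustrate the size and do not predict this trial's power.

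The primary self-care outcome and the stated sample size do not depend on this point.

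**What to change.** - Report baseline MLHFQ and knowledge by arm descriptively, without a between-group test.
- Say that the MLHFQ comparison is between arms, name the correction, and limit it to months 1, 2 and 3.
- Estimate the between-arm MLHFQ differences from a repeated-measures model of months 1 to 3 with baseline MLHFQ as covariate, each with a 95% CI.
- Analyse end-of-study knowledge by ANCOVA with baseline knowledge as covariate.
- Record the change before the arms are compared, so that adjustment is not chosen after an imbalance is seen.

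Naming month 3 as the single MLHFQ test would avoid the correction altogether, but it changes the question and is optional. The cost is analysis wording only: the protocol already collects every score needed.

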## Introduction

Heart failure (HF) is a complex clinical syndrome that results from any structural and functional impairment of ventricular filling or ejection of blood. Based on left ventricle dysfunction and the left ventricle ejection fraction (LVEF), HF can be categorized as preserved ejection fraction (with LVEF≥50%, known as HFpEF or diastolic HF) and reduced ejection fraction (with LVEF ≤40%, known as HFrEF or systolic HF) [1].

As a global burden, HF affects more than 37.7 million individuals worldwide [2] and is a common condition with 1%-2% total health resources allocated in high-income countries. In low- and middle-income countries (LMICs) like Iran, HF may displace infectious diseases as the major public health issue [3]. In Iran and other Asian LMICs, HF is described as a pandemic [4], the prevalence greatly increased with age and range between 0.5% to 9.0% among different cities, regardless of time distribution [5], thus supporting the need for better HF surveillance and management strategies [3]. Patients with HF can experience various clinical outcomes including mortality, morbidity, and other patient-reported outcomes [6]. Although mortality and morbidity rates are similar for HFpEF and HFrEF, the hospital admission rates in patients with HFrEF are much higher than HFpEF [7].

HF is a leading cause of hospitalizations [8], mortality [8,9], rising health care costs (over US $39 billion annually in the United States and US $53.1 billion by 2030) [2,8-10], suboptimal self-care behavior [11], and reduced quality of life (QOL) [12]. According to a recent European Society of Cardiology Heart Failure Long-Term Registry prospective observational study, the rate of all-cause mortality and hospitalization at one-year follow-up was 8.1% and 28.2%, respectively [13]. Compared to Western countries, patients with HF in Asia and Iran are younger, have more severe signs and symptoms, and receive lower levels of treatment compared to the European Society of Cardiology and American College of Cardiology Foundation/American Heart Association Guidelines [14]. Moreover, Callender et al [3] reported that Iranian patients with HF experience significantly lower rates of admission (0.3%).

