### Study Measures

#### Primary Outcome

##### Self-Care Behavior

Effective self-care improvement is a priority of all clinicians caring for patients with HF [46]. In a developing country like Iran, there is a growing need to improve patient’s self-care [15]. However, there is a low rate of reported admissions for HF in Iran [3]. Thus, in contrast to previous studies where hospitalization was considered the primary outcome [21,22,30] and self-care as the secondary outcome [21,22], self-care has been identified as the primary outcome in this trial.

Self-care behavior will be measured by the Self-Care of Heart Failure Index (SCHFI) version 6.2 [47] by self-reporting at baseline and monthly intervals for 3 months. SCHFI was translated into Persian and validated for Persian speaking people by Siabani et al in 2014 [48]. It consists of 3 separate scales and 22 questions: 10 for self-care maintenance, 6 for self-care management, and 6 for self-care confidence [49]. Cronbach alpha was determined for self-care maintenance (.56), management (.64), and confidence scales (.79) [48]. Scale scores can range between 0 to 100, and a score ≥70 will be considered as adequate self-care [49]. We will ask participants to complete SCHFI by themselves at baseline and then monthly for 3 months.

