### Sample Size

In this study, the sample size was calculated based on the minimal clinically important difference (MCID) approach for self-care as measured by SCHFI for the primary outcome. No specific MCID for SCHFI was available to the best of our knowledge and based on our search of the PubMed database.

The suggested MCID for assessing dyspnea with the visual analog scale (0-100 score index) was the range 10-20 [56]. Thus, improving self-care for ≥10 scores from the baseline at the end of the study has been considered as MCID for the present study in order to reach a large sample size. According to the Jurgens et al [22] study in 2013, a mean of 70.8 for self-care in the control group at the end of study (90-days) and a fixed standard deviation of 27.2 (the largest SD) have been considered. In order to calculate sample size by G*Power free software (version 3.1.9.2), the input parameters are as following: effect size (Cohen *f*) of 0.168, the alpha error probability of .05, a statistical power of 80% to detect MCID≥10 scores between the 2 groups at the end of the study, 3 times measurement of outcome with monthly intervals, and a correlation coefficient of .5 among repeated measurements. Thus, by considering the overall attrition rates of 10%, the sample size was set at 68 participants (34 participants in each group).

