### Statistical Methods

Statisticians will prepare the data sheets to collected data. Data will be entered into the SPSS software (version 16). The Kolmogorov-Smirnov test will be used to normality. A transformation approach will be used to handle non-normal distribution. For the between-group comparison of continuous and categorical baseline characteristics, independent *t* test and chi-square test will be used. For categorical variables between the 2 groups, the two-tailed Fisher exact test will be used instead of the chi-square test in the case of too small expected cell frequencies. A *P* value <.05 will be considered statistically significant.

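### At the admission rates the protocol cites, the promised hazard ratio for hospitalization may not be computable, and no finite effect estimate is planned in its place

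*Protocol article*

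**What the plan says.** In the protocol article, Secondary Analysis describes hospitalization by the median of admissions and by Kaplan-Meier curves, which it calls descriptive. For the comparison, "a log-rank test will be used to detect the significance difference between the 2 groups. A hazard ratio will be reported with 95% CI". Statistical Methods sets the significance threshold at P<.05.

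The Introduction says of a European registry that "the rate of all-cause mortality and hospitalization at one-year follow-up was 8.1% and 28.2%, respectively", and gives a much lower admission figure of 0.3% for Iranian patients without stating the period. Under Self-Care Behavior, the reason for not making hospitalization the primary outcome is that "there is a low rate of reported admissions for HF in Iran".

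Statistical Methods does have a small-count rule: "the two-tailed Fisher exact test will be used instead of the chi-square test in the case of too small expected cell frequencies". Secondary Analysis does not apply it to hospitalization, although Table 1 codes that outcome as yes/no. The sample size of 68 (34 per arm) was derived for self-care. No event count is stated for hospitalization.

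**The concern.** A hazard ratio needs at least one event in each arm. With none in one arm the estimate is 0 or infinite and the usual interval is not finite; with none in either arm there is nothing to estimate. The protocol regards admissions as rare, follows 68 patients for only 3 months, and still names the hazard ratio as its effect measure for a stated secondary objective.

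If an arm has no admission, the authors must choose another estimate after seeing the data. This is most likely when the test is significant, because with few events significance needs an extreme split. The other planned numerical summary, the median of admissions, does not fill the gap.

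**Working it through.** **Plan's own figure.** There is none for hospitalization. The 68 comes from the self-care calculation and reproduces in the repeated-measures interaction (or within-factor) form: λ = f²·N·m/(1−ρ) = 0.168² × 60 × 3/0.5 = 10.2 gives power 0.81, and 60/0.9 = 66.7, made even at 68. It serves here only as the denominator.

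**Inputs.** 34 per arm (Sample Size); 3 months of follow-up (Abstract, Methods); 28.2% at one year and 0.3% (Introduction). Assumptions: constant hazard, and each rate taken in turn as the control-arm risk.

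**Expected first admissions (equal risk in both arms).**
- 28.2% per year: p = 1 − (1 − 0.282)^(1/4) = 0.0795, and 68 × 0.0795 = 5.4. With 61 to 62 completers after 10% attrition it is 4.8 to 4.9.
- 0.3%: 68 × 0.003 = 0.2 if the figure covers the 3 months, or about 0.05 if it is annual.

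**Chance that at least one arm has no admission.** With q = 1 − (1 − p)^HR for the intervention arm, a = (1 − p)^34 and b = (1 − q)^34, the chance is a + b − ab.

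| 3-month control risk | HR = 1 | HR = 0.5 |
|---|---|---|
| 0.3% | 99.1% | 99.5% |
| 7.95% (28.2% per year) | 0.060 + 0.060 − 0.004 = 11.6% | 0.060 + 0.245 − 0.015 = 29.0% |
| 12% | 2.6% | 12.5% |
| 20% | 0.1% | 2.3% |

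With 31 per arm at the European rate, simulation gives 15% and 33%.

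**Which splits are significant (34 per arm, no earlier censoring).** For a k v 0 split the log-rank statistic is (ΣU)²/ΣV, with r = (34 − i)/(68 − i), U = 1 − r and V = r(1 − r), summed over i = 0 to k − 1. The two-sided Fisher P is 2·C(34,k)/C(68,k).

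| Split | Log-rank P | Fisher P |
|---|---|---|
| 0 v 4 | 2.046²/0.999 = 4.19, P = .041 | .114 |
| 0 v 5 | 2.577²/1.248 = 5.32, P = .021 | .053 |
| 0 v 6 | .011 | .025 |

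A 5 v 1 split gives a log-rank P of .084 to .096, depending on the order of events; 6 v 1 gives .044 to .052. So with 4 to 6 admissions the test is significant only when one arm has none, and at 7 a split of 6 v 1 is borderline.

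**How often this occurs at 28.2% per year.** Summing the binomial probabilities of all k v 0 splits with k ≥ 4, in either direction, gives 3.4% of trials at HR = 1 and 7.2% at HR = 0.5. In simulation (40,000 trials per scenario) the log-rank test is significant in 5.1% and 8.9% of trials. The share of significant results with no finite hazard ratio is therefore about 3.4/5.1 = 67% and 7.2/8.9 = 81%.

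**Median of admissions.** Read as admissions per patient, it is 0 unless at least half of an arm (17 of 34) is admitted, so at a risk of about 8% it is 0 in both arms.

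**The case against.** The protocol adopts no admission rate. One of its two figures is European and the other has no period. The Introduction also points to higher risk: more admissions in reduced than in preserved ejection fraction, and more severe symptoms in Iranian patients. At a 20% 3-month risk the difficulty nearly vanishes. This stands: the event count is a range resting on assumed rates, not a forecast of about 5.

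A reader might infer that the log-rank test is invalid here and will produce false claims of fewer hospitalizations. The calculations do not support that. Its type I error at the European rate is 5.1% with 34 per arm and 4.9% with 31. Part of the gap between .021 and .053 at 0 v 5 is the conservatism of the exact test. A split of 0 v 4 or 0 v 5 favouring the intervention arises in only 1.4% of trials at HR = 1 and 5.7% at HR = 0.5. Replacing the log-rank test by an exact one would be a trade-off, not a correction.

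Sparse-event fallbacks are often left to an analysis plan, and the Fisher rule could be read to cover the yes/no outcome in Table 1. But Secondary Analysis names the hazard ratio as the effect measure and does not invoke that rule. The point concerns a stated choice that fits badly with the rates the protocol cites, not an omitted detail.

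**Conclusion.** The concern holds for the effect estimate, not for the validity of the test. At 28.2% per year and 34 per arm, the hazard ratio has no finite estimate or interval in about 12% (HR = 1) to 29% (HR = 0.5) of trials, and in roughly 70 to 80% of significant log-rank results. At 0.3% this is the case in at least 99% of trials; at a 20% 3-month risk, in about 2% or fewer. The planned median would be uninformative at either cited rate. These figures assume a constant hazard and that a cited rate applies to this clinic.

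A narrower point remains on the P value: at 0 v 4 and 0 v 5 the log-rank result falls below .05 and Fisher's does not. Readers should see that when it happens, but it does not show an inflated error rate. Since the outcome is secondary, this is an inexpensive improvement, not a fault that undermines the trial.

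**What to change.** In Secondary Analysis, make the reported effect the number and percentage of patients with at least one admission in each arm, with the risk difference and its Newcombe 95% CI. The yes/no coding in Table 1 already supplies the data, and the interval is finite with zero events. For 0/34 v 5/34 it is −14.7 percentage points (−30.1 to −1.6); for 0/34 v 4/34, −11.8 (−26.6 to 0.6); for no events in either arm, 0 (−10.2 to 10.2).

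Keep the Kaplan-Meier curves and the log-rank test. Give a hazard ratio only by a method that exists when one arm has no event, for example Firth-penalized Cox regression with a profile-likelihood interval, and state that none is reported if neither arm has an admission. Optionally, extend the small-count rule in Statistical Methods so that a Fisher or permutation log-rank P is shown beside the log-rank P when admissions are few.

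The cost is a few sentences and slightly more analysis work, possibly outside the SPSS version 16 that the protocol names. No new data or patients are needed. If the exact P is shown it will be less favourable at small counts, and it can disagree with the interval, as at 0 v 5, so the plan should say which one governs the conclusion.
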